**Clinical interview**						
	NSSI thoughts, NSSI behaviors, DSM-5^f^ NSSI disorder, suicide ideation, suicide plan, suicide attempt, age of onset, frequency, recency, functions of NSSI, experience of pain during NSSI, and impact of NSSI^b^	Adapted Self-Injurious Thoughts and Behaviors Interview		Original [64] and Dutch translation [22]	29-41; mixed	
	Self-efficacy to resist suicide^b^	Self‑Efficacy to Avoid Suicide Action Scale		Original [86] and Dutch translation [27]	6; 10-point scale	
	Major depressive disorder, alcohol use disorder, substance use disorder, panic disorder, generalized anxiety disorder, posttraumatic stress disorder, and eating disorders	Structured Clinical Interview for DSM-5		Original [66] and Dutch translation [105]	18-310; mixed	

^a^UPPS-P: urgency, premeditation, perseverance, sensation seeking, and positive urgency.

^b^Reassessed in the web-based follow-up surveys 4 and 12 weeks after the 28-day real-time monitoring period.

^c^NSSI: nonsuicidal self-injury.

^d^FBT: forward-backward translation.

^e^N/A: not applicable.

^f^DSM-5: Diagnostic and Statistical Manual of Mental Disorders, Fifth Edition.

#### Phase 1: Web-Based Baseline Assessment of Mental Health Professionals

Each mental health professional also provides informed consent the first time and completes a brief survey assessing sociodemographic (age and gender) and professional information (profession, level of education, and years of experience). In addition, they can provide the research team with 1 to 3 additional EMA questions when considered relevant for a specific individual.

#### Phase 2: EMA Sampling Design and Content

The second phase starts on the morning after the baseline assessment. It involves a 28-day EMA protocol that consists of (1) six semirandom regular EMA surveys administered on average every 2 hours during waking hours between 10 AM and 9:30 PM, (2) three burst EMA surveys spaced at a higher frequency of 5 to 10 minutes apart in the 30 minutes after intense NSSI urges are reported in the regular EMA surveys (score of ≥5 on a 7-point item), and (3) event registrations via a push button to record the timing of NSSI behavior. Figure 3 shows the sampling schedule of the DAILY project, which includes a minimum of 168 regular EMA surveys and a theoretical maximum of 672 EMA surveys (when a burst sequence is triggered during each regular survey). To ensure that we capture people in their ongoing activities and to avoid retrospective reporting, participants must register responses to the regular EMA within 15 minutes of receipt and to the burst EMA surveys within 5 minutes of receipt. In case of nonresponse to the regular EMA surveys, 1 reminder is sent after 10 minutes. After the first day and each week subsequently, a team member telephoned the participants to check whether everything is going well, provide feedback about study compliance, and respond to concerns or difficulties concerning the app and the self-monitoring.

Table 2 presents the EMA constructs and items in the DAILY project, including emotions and cognitions (block A); contextual information and social appraisals (block B); NSSI thoughts, NSSI urges, self-efficacy to resist NSSI, and NSSI behavior (block C); and the screening of other self-damaging behaviors and experienced momentary burden (block D, part 1). EMA items were as much as possible selected or modified from prior EMA studies and conventional survey questionnaires [27,86,90,106-108]. Questions are branched so that participants only have to complete relevant EMA items (eg, social appraisals are context specific). The order in which emotions and cognitions are presented is randomized within individuals across the EMA surveys (because these items are not conditional on each other). Specific emotions for negative and positive affect are selected because they represent all 4 quadrants of the affective circumplex defined by valence and arousal dimensions [109]. All continuous EMA items are assessed on 7-point rating scales ranging from not at all or absent to very much or very strong (Table 2). Although NSSI behavior is assessed retrospectively during each EMA survey (ie, “Since the last beep, have you deliberately hurt yourself without wanting to die?”), participants are instructed to register the timing of NSSI behavior through an event marker. This occurred on a wearable wireless device (Chill Band +; IMEC International) for the first 12 participants. However, owing to practical and technical issues with these devices, the remaining participants used an event registration push button in the m-Path app [68].

During each regular EMA survey, we also screened whether participants experienced thoughts, had an urge, or engaged in 6 other self-damaging behaviors, including restrictive eating, purging, binge eating, STB, binge drinking, and smoking cannabis (block D, part 1). If they answer ≥1 of these self-damaging behaviors affirmatively, additional items assess thoughts, urges, behavior engagement, and self-efficacy to resist the endorsed behavior(s) (block D, part 2, Table 3). Finally, participants rate the extent to which they consider an EMA survey burdensome. The regular EMA surveys include 28 to 31 items (excluding optional individual-specific questions), with 4 additional items for each of the other self-damaging behaviors endorsed on the screening item (Table 3). The burst EMA surveys include 21 to 22 items, assessing only emotions and cognitions (block A) and NSSI outcomes (block C).

**Figure 3 figure3:**
[figure not shown]
Graphical overview of the ecological momentary assessment (EMA) sampling schedule. (A) Six semirandom regular EMA surveys taken on average every 2 hours during waking hours between 10 AM and 9:30 PM. (B) Three burst EMA surveys spaced at a higher frequency of 5 to 10 minutes apart in the 30 minutes after intense nonsuicidal self-injury (NSSI) urges in the regular EMA surveys. (C) Event registrations via a push button to register the timing of NSSI behavio.

**Table 2 table2:** Ecological momentary assessment (EMA) constructs and items.

EMA constructs^a^			Items		Response category
**Block A: emotions and cognitions (17 items)**					
	Momentary negative affect	[Right now]: “I feel anxious,” “I feel stressed,” “I feel irritated,” “I feel sad,” and “I feel insecure”		7-point scale (ranging from not at all to very much)	
	Momentary positive affect	[Right now]: “I feel cheerful” and “I feel relaxed”		7-point scale (ranging from not at all to very much)	
	Momentary emptiness	[Right now]: “I feel empty”		7-point scale (ranging from not at all to very much)	
	Momentary loneliness	[Right now]: “I feel lonely”		7-point scale (ranging from not at all to very much)	
	Momentary emotion dysregulation	[Right now]: “My emotions are overwhelming me”		7-point scale (ranging from not at all to very much)	
	Momentary rumination	[Right now]: “I am repeatedly thinking about the same problem”		7-point scale (ranging from not at all to very much)	
	Momentary self-criticism	[Right now]: “I am disappointed in myself”		7-point scale (ranging from not at all to very much)	
	Momentary other-criticism	[Right now]: “I am disappointed in others”		7-point scale (ranging from not at all to very much)	
	Momentary body image	[Right now]: “I am satisfied with the way I look” and “I feel at ease in my body”		7-point scale (ranging from not at all to very much)	
	Momentary identity	[Right now]: “I doubt who I am” and “I know what I stand for”		7-point scale (ranging from not at all to very much)	
**Block B: contextual information and social appraisals (5-7 items)**					
	Momentary situational context	“Where are you?”		(a) At home; (b) at a friend’s or family’s place; (c) school or work; (d) car, train, bus; (e) other indoors; (f) other outdoors	
	Momentary activity	“What were you doing just before the beep?” (If g) “Please describe briefly what you are doing”		(a) Nothing, (b) work or studying, (c) household chores, (d) conversation, (e) leisure active (eg, sports), (f) leisure passive (eg, watching television), (g) something else	
	Momentary appraisal of activity	“I enjoy this activity”		7-point scale (ranging from not at all to very much)	
	Momentary social context	“Are you alone or with others?” (If b) “Who are you with physically?” (If c) “Who are you with online?”		(a) Alone, (b) others physically, (c) others on the web (a) Partner, (b) family, (c) friends, (d) colleagues, (e) acquaintances, (f) other patients, (g) unfamiliar people	
	Momentary appraisal of social context	(If a): “I like being alone” (If b): “I enjoy the company of these people” (If c): “I feel connected to those I am online in contact with”		7-point scale (ranging from not at all to very much) 7-point scale (ranging from not at all to very much) 7-point scale (ranging from not at all to very much)	
**Block C: NSSI^b^ (4-5 items)**					
	Retrospective thoughts	“Since the last beep, have you considered deliberately hurting yourself without wanting to die?”		7-point scale (ranging from not at all to very much)	
	Momentary urge	“Right now, how strong is the urge present to hurt yourself without wanting to die?”		7-point scale (ranging from absent to very strong)	
	Retrospective behavior	“Since the last beep, have you deliberately hurt yourself without wanting to die (for example, cut, scratched, or hit yourself)?”		(a) No, (b) yes	
	Retrospective behavior (method)	(If b): “How have you self-injured?”		(a) Cutting or carving, (b) scratching, (c) hitting, (d) burning, (e) biting, (f) head banging, (g) wound interfering, (h) other method (describe briefly)	
	Momentary self-efficacy to resist	“Right now, how confident are you that you can resist engaging in NSSI?”		7-point scale (ranging from not at all to very)	
**Block D (part 1): screen other self-damaging thoughts or behaviors and interference (2 items)**					
	Screen comorbid thoughts or behaviors	“Indicate all other behaviors you thought about or engaged in since the last beep, or for which you have an urge right now”		(a) Restrictive eating, (b) binge eating, (c) vomiting deliberately, (d) killing myself, (e) binge drinking, (f) using cannabis, (g) none of these	
	Interference	“This beep disturbed me.”		7-point scale (ranging from not at all to very much)	

^a^Blocks A to D are assessed in the regular EMA surveys. Blocks A and C are only assessed in the burst EMA surveys.

^b^NSSI: nonsuicidal self-injury.

**Table 3 table3:** Ecological momentary assessment of other self-damaging behaviors^a^.

Block D (part 2): Other self-damaging behaviors and items				Response category
**Restrictive eating (4 items)**				
	**Retrospective thoughts**			
		Since the last beep, have you thought about eating less to control your weight?	7-point scale (ranging from not at all to very much)	
	**Momentary urge**			
		Right now, how strong is the urge to eat less to control your weight?	7-point scale (ranging from absent to very strong)	
	**Retrospective behavior**			
		Since the last beep, have you eaten less to control your weight?	(a) No, (b) yes	
	**Momentary self-efficacy to resist**			
		Right now, how confident are you that you can resist eating less to control your weight?	7-point scale (ranging from not at all to very)	
**Binge eating (4 items)**				
	**Retrospective thoughts**			
		Since the last beep, have you thought about eating an unusually large amount of food?	7-point scale (ranging from not at all to very much)	
	**Momentary urge**			
		Right now, how strong is the urge to eat an unusually large amount of food?	7-point scale (ranging from absent to very strong)	
	**Retrospective behavior**			
		Since the last beep, have you experienced a binge-eating episode?	(a) No, (b) yes	
	**Momentary self-efficacy to resist**			
		Right now, how confident are you that you can resist eating an unusually large amount of food?	7-point scale (ranging from not at all to very)	
**Purging (4 items)**				
	**Retrospective thoughts**			
		Since the last beep, have you thought about vomiting deliberately?	7-point scale (ranging from not at all to very much)	
	**Momentary urge**			
		Right now, how strong is the urge to vomit deliberately?	7-point scale (ranging from absent to very strong)	
	**Retrospective behavior**			
		Since the last beep, have you vomited deliberately?	(a) No, (b) yes	
	**Momentary self-efficacy to resist**			
		Right now, how confident are you that you can resist vomiting deliberately?	7-point scale (ranging from not at all to very)	
**Suicidality (4 items)**				
	**Retrospective thoughts**			
		Since the last beep, have you thought about killing yourself?	7-point scale (ranging from not at all to very much)	
	**Momentary urge**			
		Right now, how strong is the urge to kill yourself?	7-point scale (ranging from absent to very strong)	
	**Retrospective behavior**			
		Since the last beep, have you made a suicide attempt?	(a) No, (b) yes	
	**Momentary self-efficacy to resist**			
		Right now, how confident are you that you can resist attempting suicide?	7-point scale (ranging from not at all to very)	
**Binge drinking (4 items)**				
	**Retrospective thoughts**			
		Since the last beep, have you thought about consuming an unusually large amount of alcohol?	7-point scale (ranging from not at all to very much)	
	**Momentary urge**			
		Right now, how strong is the urge to consume an unusually large amount of alcohol?	7-point scale (ranging from absent to very strong)	
	**Retrospective behavior**			
		Since the last beep, have you consumed an unusually large amount of alcohol?	(a) No, (b) yes	
	**Momentary self-efficacy to resist**			
		Right now, how confident are you that you can resist consuming an unusually large amount of alcohol?	7-point scale (ranging from not at all to very)	
**Cannabis use (4 items)**				
	**Retrospective thoughts**			
		Since the last beep, have you thought about smoking cannabis?	7-point scale (ranging from not at all to very much)	
	**Momentary urge**			
		Right now, how strong is the urge to smoke cannabis?	7-point scale (ranging from absent to very strong)	
	**Retrospective behavior**			
		Since the last beep, have you smoked cannabis?	(a) No, (b) yes	
	**Momentary self-efficacy to resist**			
		Right now, how confident are you that you can resist smoking cannabis?	7-point scale (ranging from not at all to very)	

^a^These other self-damaging behaviors are only assessed when screened positively in block D (part 1; Table 2) in the regular ecological momentary assessment surveys.

#### Phase 2: Safety Measures and Risk Monitoring

Participants are provided a 1-page information sheet with the contact information of the research team (study-specific telephone number and email address) as well as suicide and crisis hotlines during the baseline enrollment (phase 1). Although research suggests no reactivity or iatrogenic effects of repeated questioning about self-injurious thoughts and behaviors [110-112], there should be a proper safety protocol that not only matches participants’ needs [113] but also does not inadvertently defeat the study’s observational purpose [19,114]. Therefore, several measures are in place to support and safeguard participants’ safety during the EMA period. First, an automatic pop-up screen with resources is shown at the end of a regular EMA survey whenever a participant indicates an intense urge for NSSI or any other self-damaging behavior (response 6 or 7 on a 7-point scale). This pop-up item contains either standard resources that signpost participants to relevant support organizations, family and friends, and their mental health professional or the personal resources provided by the participant during phase 1 (randomized within individuals across surveys with an equal probability of 0.5).

Second, a safety protocol is activated whenever a participant reports having attempted suicide or is at imminent risk for attempting suicide, operationalized as having an intense urge to attempt suicide (response 6 or 7 on a 7-point scale) combined with momentary low self-efficacy to resist this suicidal urge (responses 1-3 on a 7-point scale). A second automatic pop-up screen is triggered whenever this response pattern occurs, encouraging participants to provide more in-the-moment information within an open text field. After submitting this item (even when left blank), this response pattern issues an alert to the research team (ie, flagged email to the study account that is consistently monitored during recruitment hours). This information is then shared via telephone with clinical staff members on duty at the care facility for inpatients, after which they take appropriate action. The participating mental health professional also receives an email with this information. When the safety alert concerns an outpatient, a licensed clinical psychologist from the research team conducts the risk assessment by telephone. For minors, the parents or legal guardians are also contacted by telephone when a minor participant cannot be reached or when the clinical psychologist of the research team considers this necessary after a risk assessment.

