Phase 1 concludes with an orientation and training on completing the EMA protocol via m-Path, a user-friendly and secure smartphone app and platform created by researchers at KU Leuven that is General Data Protection Regulation (GDPR)–compliant for real-time and real-world data collection [68]. We assign all participants a study alias to ensure that no identifying information is shared with the software platform. All communication between participants’ smartphones and the server is end-to-end encrypted and securely uploaded after each interaction [68]. Participants without a smartphone are loaned a device with a prepaid data plan for data collection. Study staff help participants to download the app on their phone (Android or IOS) or the loaned device (Android), discuss the EMA protocol’s content and procedures, answer participants’ questions, and initiate a practice EMA survey for the participant. Phase 1 takes approximately 3 to 4 hours to complete.

**Table 1 table1:** Overview of the variables assessed in the baseline survey battery and clinical interview.

Baseline assessment			Measure	Source		Items, n; response scale

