#### Expected Sample Size

We intend to recruit 120 individuals seeking treatment. Analyses that include 100 to 120 participants will yield sufficient statistical power (≥0.80) to detect within-person effects as small as 0.07 to 0.09 in multilevel autoregressive models. These power calculations were conducted using Monte Carlo simulations with the following conservative estimates [135]: a 1:0.67 ratio of random intercept to within-person residual deviation, a 1:0.25 ratio of random intercept to random slope SD, first-order and slope-intercept correlations of 0.5, and compliance of 60% to the regular EMA surveys. Recent studies have used pooled machine learning models with fewer observations and participants [127]. In addition, it has been shown recently that as few as 60 assessments from 25 individuals allow robust estimation of general, shared, and person-specific temporal associations in intensive longitudinal data [136].

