### Limitations

Although EMA is a powerful methodology that can now more readily be used to provide previously unavailable information about the course, within-person predictors, comorbidity patterns, and clinical outcomes of NSSI in daily life [19], it is crucial to consider the implications and limitations of the protocol used and the design when interpreting the project’s findings. First, although measures are in place to ensure that recruitment is inclusive and geographically representative, with recruitment sites spread across the entire Flanders region of Belgium, it should be acknowledged that we use convenience sampling, with the targeted sample comprising individuals currently receiving mental health treatment. This implies that the findings should not be generalized to nonclinical populations because the short-term course of NSSI will likely differ in severity for community samples. Relatedly, adolescents can only participate from the age of 15 years, meaning that the findings are not generalizable to early adolescents (aged 10-14 years) and should be studied in this population. Second, the intensive sampling scheme matches the project’s research objectives but involves a higher burden than traditional longitudinal studies (typically 1-5 surveys months to years apart) and most EMA studies (typically lasting 1 week) [26]. Although scholars have observed increased burden with longer questionnaires but not with increased sampling frequency among community samples [141], it should be investigated to what extent the current EMA sampling scheme and duration were considered feasible by all individuals seeking treatment. Third, we implemented safety measures for NSSI and other self-damaging behaviors (including the monitoring of suicide risk) based on prespecified cutoffs of momentary urges and low self-efficacy to resist a behavior. Future research would benefit from evaluating risk thresholds and the utility of different safety measures (eg, personal vs standard message and human-led vs automatic action) at varying risk levels for self-damaging behaviors.

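### The suicide-risk alert is sent only after a further pop-up is submitted, so a participant who reports an attempt or imminent risk and stops there may raise no alert

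*Protocol article*

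**What the plan says.** Under Phase 2: Safety Measures and Risk Monitoring, the protocol article activates a safety protocol whenever a participant reports a suicide attempt or is at imminent risk. Imminent risk is defined entirely by two answers: a suicide urge of 6 or 7, together with self-efficacy to resist of 1 to 3.

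The article then describes how this is carried out. "A second automatic pop-up screen is triggered whenever this response pattern occurs", and that screen invites the participant to write more in an open text field. Next, "After submitting this item (even when left blank), this response pattern issues an alert to the research team". The alert is a flagged email to the study account. For inpatients it leads to a telephone call to staff on duty. For outpatients it leads to a telephone risk assessment by a licensed psychologist on the research team.

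In Table 3, the attempt item reads "Since the last beep, have you made a suicide attempt". The suicide urge and self-efficacy items ask about the present moment. All of these items appear in regular surveys only, after a positive screen. The schedule is "six semirandom regular EMA surveys administered on average every 2 hours during waking hours between 10 AM and 9:30 PM".

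**The concern.** The principle and the mechanism do not match. The principle is activation whenever the risk is reported. The mechanism requires the report plus the submission of one more screen. That extra step comes just after the participant has disclosed an attempt, or a strong urge that they doubt they can resist.

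The step is not needed for detection. The Limitations section describes the safety measures as "based on prespecified cutoffs of momentary urges and low self-efficacy to resist a behavior", which are closed-ended answers already given by then. Because a blank text field is acceptable, the team evidently does not need the text in order to act.

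At stake is the start of the human response. Without the alert, neither the call to ward staff nor the psychologist's risk assessment is set in motion by that survey. This is a participant-safety point and changes no statistical figure.

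**Working it through.** The article gives no rate or figure to reproduce, so the check traces the alert path through the text and adds the timing that follows from the survey schedule.

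1. **Condition for activation.** Reported attempt = yes, or suicide urge 6–7 with self-efficacy 1–3 (Safety Measures and Risk Monitoring). Both limbs are fully determined by the survey answers.

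2. **Order of steps.** Qualifying answers, then the second pop-up, then submission of the pop-up, then the email alert. The parenthesis about blank entries removes the need to write text. It does not remove the need to submit.

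3. **Other automatic routes to the team.** Each remaining measure in the article was checked:
   - The first pop-up shows resources after an intense urge. It is not described as notifying anyone, and it is tied to urges, not to a reported attempt.
   - Telephone calls follow the first day and then come weekly. Risk answers do not trigger them.
   - Data are "securely uploaded after each interaction". What counts as an interaction is not defined, and no alert on uploaded answers, or review of them, is described.
   - A psychologist is on call outside office hours, but no separate route is given by which that person would learn of the answers.

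   None of these is stated to act when the second pop-up is left unsubmitted.

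4. **Recovery at the next regular survey.** The two limbs behave differently:
   - *Urge limb.* The items are momentary. If the state persists, the participant answers the next regular survey and the screen is again positive, the sequence can start again.
   - *Attempt limb.* The item looks back only to the previous beep, so an attempt reported at survey *k* lies before the window of survey *k* + 1. Only a new attempt, or a qualifying urge with low self-efficacy, would restart the sequence.

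5. **Timing of that next survey.**
   - Within the day: on average about 2 h.
   - Overnight, beep to beep: the last survey is no later than 9:30 PM and the next no earlier than 10 AM. From 9:30 PM to midnight is 2.5 h, and from midnight to 10 AM is 10 h, so 2.5 + 10 = 12.5 h at least.
   - The Limitations section gives 10 PM as the end of scheduled surveys. With that limit the minimum is 2 + 10 = 12 h.
   - After the last regular survey of day 28 there is no further regular survey.

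6. **Frequency of non-submission.** The article gives nothing from which to estimate it, so no rate is assigned.

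**The case against.** The strongest reply has three parts.

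First, this is a condensed article. Time-outs, handling of unfinished surveys and dashboard checks are details that a full protocol or safety procedure would normally hold. A reader might infer that no fallback exists. The article does not support that; it shows only that none is described here. The submission step, however, is stated text and not an omission.

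Second, the sentence may describe the usual sequence without excluding an alert when the pop-up is abandoned, since the same paragraph speaks of activation whenever risk is reported. That reading is possible. If it is correct, the sentence describing the trigger misdescribes the system and should be amended.

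Third, the gap is narrow and other protection exists. One tap is enough, with no text required. Participants hold the study telephone number and crisis contacts, they are in treatment at recruitment, minors must keep a treating professional throughout monitoring, and inpatients have staff on duty. All of this stands and lowers the exposure. These measures can bring help or let the team find out. They do not give the team immediate, automatic notice that this participant has just reported an attempt or imminent risk.

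Two stronger readings should be resisted. A reader might take the planning assumption of "compliance of 60% to the regular EMA surveys" and conclude that 40% of the follow-on surveys would be missed. That figure is an average assumed for a power simulation and does not describe response just after a disclosed attempt or urge. A reader might also hold it against the burst surveys that they carry no suicide items. Bursts are triggered by self-injury urges and were never the suicide-monitoring channel.

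**Conclusion.** The point holds in a limited form. As written, the alert depends on one submission beyond the answers that define the risk. A participant who stops at that screen may raise no alert.

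The exposure is confined to participants who leave before submitting, at an unknown rate. If that happens, the urge limb has a later chance at the next answered regular survey, on average about 2 h later or at least 12.5 h later overnight (12 h under the 10 PM limit). A reported attempt is not asked about again.

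This rests on reading the trigger sentence literally and on the absence of any other automatic route in the article. Confidence is medium, because a safety procedure that is not shown may already cover the case. The change is still worth making: a single failure could delay the response to a reported suicide attempt, and the remedy is small.

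**What to change.** Issue the alert when the qualifying answers are recorded: attempt = yes, or suicide urge 6–7 with self-efficacy 1–3. If the app cannot do this mid-survey, which the article does not say, send the alert automatically after a short time-out when the pop-up is not submitted. Keep the free-text screen as a supplement and append any text to the alert afterwards. If the system already works this way, correct the sentence in the safety section.

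The cost is a change to the trigger in the app, a test of it, and one sentence in the protocol. There will be a few more alerts without context, which the plan already accepts for blank submissions. Deterrence to reporting may rise slightly; the Limitations section already acknowledges possible underreporting because staff contact participants. Suicidal thoughts and behaviors are a secondary outcome and recruitment began in June 2021, so the date of any change should be recorded to allow reporting before and after it to be compared. The self-injury items and the planned analyses stay as they are.
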